## 4. EXCITING-ILD Registry Objectives

The overall objective of the EXCITING-ILD registry is to generate sociodemographic and medical data relating to ILDs, which will help to answer epidemiological and disease-related questions that will be important in Germany. This registry will also provide an important database for health economic and health services research questions.

Specific objectives of the EXCITING-ILD registry will be to determineclinical, disease-related characteristics of ILD patients;diagnostic procedures for the identification of ILDs;the clinical management of different (sub)types of ILD in real-world practice;the outcome of different types of ILDs and of ILD-related therapies from all forms of healthcare facilities.

Main endpoints, reflecting the objectives of this registry, areincidence and prevalence of ILD subtypes;(disease-related) characteristics of ILD patients;diagnostic procedures for the identification of ILDs;management of different (sub)types of ILD;the outcome of different types of ILDs and of ILD-related therapies measured as time to death;ILD management as analysed by the kind and frequency of pharmacological and nonpharmacological therapies;prognostic factors in different ILDs;lung functional parameters.

Healthcare utilisation will be assessed as a basis for cost estimates for the following healthcare services:outpatient treatment;hospitalisation due to ILD;temporary occupational disability;medication;additional therapies;medical aids and appliances;participation in rehabilitation programmes.

Sociodemographic data variables aregender;year of birth;country of birth;place of residence;profession;incapacitated for work;health insurance coverage (statutory, private, and granting aid).

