### 5.7. Statistical Methods

A Statistical Analysis Plan (SAP) has been developed prior to initiation of the registry and final analysis of the trial will be performed by syneed medidata GmbH. All observational data collected will be analysed descriptively using established statistical and epidemiological methods. Time to death will be analysed by means of Kaplan-Meier survival analysis. In addition, further secondary inferential methods may be specified in the SAP if deemed appropriate. If not specified otherwise in the SAP, missing data will not be imputed. Subjects with incomplete data will be included in the analysis and for each variable; the number of subjects with missing data will be reported. Interim analyses comprising descriptive summaries of the data collected in the CRF will be produced every 3 months.

*Sample Size*. In the initial phase of 12 months, enrolment of up to 350 patients is anticipated. At the end of year 2, it is anticipated that up to 600 patients will be enrolled. This sample size (*n* = 350) allows for a log-rank test at a fixed time given a hazard ratio ≤0.68 at alpha = 0.05 with a power of 95%. Equally, this allows for estimating an event with 50% frequency at a confidence interval of ±5% at a 95% confidence level. All subjects with at least one documented postbaseline visit will be entered into the full analysis set (FAS). Further analysis sets may be defined in the SAP.

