## Figures and Tables

**Figure 1 fig1:**
[figure not shown]
Classification of ILDs. PAP: pulmonary alveolar proteinosis, LAM: lymphangioleiomyomatosis, and PLHC: pulmonary Langerhans cell histiocytosis. Adapted from the American Thoracic Society, European Respiratory Society International Multidisciplinary Consensus Classification of the Idiopathic Interstitial Pneumonias, Am J Respir Crit Care Med. 2002, and Travis et al. Am J Respir Crit Care Med. 2013 [2, 3].

**Table 1 tab1:** Comparison of the distribution of interstitial lung diseases (ILDs) in respiratory physicians' prospective registries [18].

	Flanders (Belgium) (1992–1996)		Germany (1995)	Italy (1997–1999)	Spain/RENIA (1998–2000)	Spain/SEPAR (2000-2001)	Greece (2004)	
	Prevalent cases	Incident cases	Incident cases	Prevalent cases	Incident cases	Incident cases	Prevalent cases	Incident cases
Subjects (*n*)	362	264	234	1138	744	511	967	254
Idiopathic								
Sarcoidosis	112 (31)	69 (26)	83 (35)	344 (30)	87 (12)	76 (15)	330 (34)	60 (23)
IPF/IIP	62 (17)	50 (19)	76 (32)	417 (37)	287 (39)	215 (42)	234 (24)	66 (25)
COP/BOOP	10 (2.3)	9 (3.4)	16 (6.8)	57 (5.0)	38 (5.1)	53 (10)	51 (5.3)	18 (7.0)
(C)EP	9 (2.2)	7 (2.7)		27 (2.3)	—	—	21 (2.2)	7 (2.7)
CTD	27 (7.5)	19 (7.2)	5 (2.1)	—	69 (9.3)	51 (19)	120 (12)	30 (12)
Vasculitis^*∗*^	5 (1.4)	4 (1.5)	2 (0.8)	25 (2.2)	—	—	14 (1.5)	6 (2.3)
EG/HX	13 (3.6)	7 (2.7)	—	73 (7.2)	6 (0.8)	15 (3)	37 (3.8)	7 (2.7)
Nonidiopathic								
EAA	47 (13)	32 (12)	25 (11)	50 (4.3)	38 (5.1)	34 (7)	25 (2.6)	7 (2.7)
Drug^†^	12 (3.3)	12 (5)	6 (2.6)	21 (1.8)		21 (4)	17 (1.8)	4 (1.5)
Pneumoconiosis^‡^	19 (5.0)	18 (6.8)	6 (2.6)	—	55 (7.4)	—	20 (2.0)	8 (3.1)
Variable aetiology								
Nonspecific fibrosis	33 (9.1)	27 (10)	12 (5.1)	—	69 (9.3)	—	82 (8.5)	40 (15)
Others	13 (3.8)	10 (3.8)	—	124 (11)	76 (10)	9 (2)	15 (1.5)	6 (2.3)

Data are presented as *n* (%), unless otherwise stated. RENIA: Registry of Interstitial Pneumopathies of Andalusia; SEPAR: Sociedad Española de Neumología y Cirugía Torácica; IPF: idiopathic pulmonary fibrosis; IIP: idiopathic interstitial pneumonia; COP: cryptogenic organising pneumonia; BOOP: bronchiolitis obliterans organising pneumonia (not necessarily cryptogenic); (C)EP: (chronic) eosinophilic pneumonia; CTD: connective tissue disease; EG/HX: eosinophilic granuloma/histiocytosis X; EAA: extrinsic allergic alveolitis (hypersensitivity pneumonitis).

^*∗*^Goodpasture's, granulomatosis with polyangiitis (Wegener's), Churg-Strauss, and so forth.

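### The stated ±5% precision at 95% confidence needs 385 patients, not 350; at 350 it is ±5.2 points, and the figure describes the pooled ILD cohort only

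*Protocol article*

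**What the plan says.** Section 5.7 of the Protocol article (Statistical Methods, sample size paragraph) anticipates up to 350 patients in the first 12 months. It gives two justifications for that number. The first concerns group comparison: "This sample size (*n* = 350) allows for a log-rank test at a fixed time". The second concerns precision: "this allows for estimating an event with 50% frequency at a confidence interval of ±5% at a 95% confidence level". Only the second is at issue here.

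The same paragraph adds that "At the end of year 2, it is anticipated that up to 600 patients will be enrolled" and defines the main analysis population: "All subjects with at least one documented postbaseline visit will be entered into the full analysis set (FAS". It states no rate of loss and no allowance for it.

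The precision statement names no ILD subtype, so it can refer only to all enrolled patients together. Section 4 lists several main endpoints by ILD type or subtype, among them "management of different (sub)types of ILD", the incidence and prevalence of subtypes, time to death by type of ILD, and prognostic factors in different ILDs. Other main endpoints, such as patient characteristics, diagnostic procedures and lung function, are not stated by subtype.

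**The concern.** The frequency, the half-width, the confidence level and the sample size are all stated, so the claim can be checked directly, and it does not come out. A reader who repeats the calculation gets 385 rather than 350.

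What is at stake is modest. It is one of two published reasons for the sample size, and it is wrong as written. It also does not say which population it covers. In a registry that will report much of its content by subtype, the scope of a precision figure should be plain.

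**Working it through.** **Inputs, all from Section 5.7:** frequency p = 0.50, half-width d = 0.05, two-sided 95% confidence (z = 1.96), n = 350; up to 600 by the end of year 2.

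**Step 1. Patients needed for ±5 points.**
n = z² p(1 − p) / d² = 3.8416 × 0.25 / 0.0025 = 384.16, rounded up to 385. The plan's 350 is not reproduced; 385 is 10% more.

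**Step 2. Half-width that the planned numbers give.**
Half-width = 1.96 × √(0.25/n) = 0.98/√n.
- n = 350: 0.98/18.71 = 5.24 points
- n = 385: 0.98/19.62 = 4.99 points
- n = 600: 0.98/24.49 = 4.00 points

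**Step 3. Confidence of a ±5.0-point interval at n = 350.**
z = 0.05/√(0.25/350) = 1.871, which corresponds to a two-sided confidence of about 93.9%.

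**Step 4. Could another convention give 350?**

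| Method, p = 0.50, ±5 points | n needed |
|---|---|
| Wald, 95% | 385 |
| Wilson or Agresti-Coull, 95% | 381 |
| Jeffreys, 95% | 382 |
| Clopper-Pearson, 95% | 402 |
| Wald with continuity correction, 95% | 404 |
| Wald with z rounded to 2 | 400 |
| Wald, 90% interval | 271 |

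None gives 350. A finite-population correction would do so only for a source population of about 3,930, which the article does not state. A frequency of about 35% (or 65%) would also do so, since 3.8416 × 0.35 × 0.65 / 0.0025 = 349.6, but the plan says 50%.

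**Step 5. Loss from the full analysis set.** The article gives no rate, so these are assumptions. If 10%, 20% or 30% have no post-baseline visit:
- 350 enrolled leaves 315, 280 or 245, with ±5.5, ±5.9 or ±6.3 points
- 600 enrolled leaves 540, 480 or 420, with ±4.2, ±4.5 or ±4.8 points

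**Step 6. Illustration by subtype.** The article plans no case mix. As an assumption, take the German 1995 column of Table 1: 83 sarcoidosis and 76 IPF/IIP among 234 incident cases.
- Sarcoidosis: 350 × 83/234 = 124 patients, ±8.8 points; 600 × 83/234 = 213, ±6.7 points
- IPF/IIP: 350 × 76/234 = 114 patients, ±9.2 points; 600 × 76/234 = 195, ±7.0 points

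Against the pooled ±5.24 at n = 350, these are 8.8/5.24 = 1.7 and 9.2/5.24 = 1.8 times as wide.

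**The case against.** The best defence is that nothing turns on the gap. The plan states precision in whole percent, and 5.24 rounds to 5. The 350 is only the first-year figure; ±5 is met once 385 patients are evaluable, and the 600 anticipated after year 2 would give ±4.0. Section 5.7 calls the analysis descriptive, so no test or decision depends on the difference. All of this stands and keeps the point minor. It does not make the sentence right, because the figure is tied to n = 350.

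A second defence is that Section 5.7 claims nothing for subtypes, and that Section 5.2 makes comparisons between ILDs depend on statistical power. That also stands. A reader might infer that the plan promises ±5% within each subtype, or that its omission of subtype precision is a fault. The text supports neither: no subtype claim is made, and subtype half-widths, interval methods and minimum group sizes can properly sit in an analysis plan that is not shown.

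A reader might also infer that subtype uncertainty is many times larger throughout. On the illustrative mix, the two largest groups, (83 + 76)/234 = 68% of patients, are less than twice as wide as the pooled figure. Much larger multiples come from the smallest cells of a single 1995 column. In that column connective tissue disease is 2.1% of cases, while other registries in Table 1 show about 7% to 19%. Section 3 itself says that the earlier German registry predates the current classification and was not truly population-based. Allowances for clustering by centre would need an intraclass correlation that the article does not give, so none is claimed here.

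**Conclusion.** The precision statement is wrong as written: 350 patients give ±5.24 points at 50% frequency and 95% confidence, and ±5 needs 385. This rests only on the plan's own inputs and on the standard formula, which treats patients as independent.

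The error is 0.24 points, or 35 patients, and it disappears at the anticipated 600 even if 30% were lost from the full analysis set (an assumed rate). It is therefore a minor correction and does not show that the registry is too small. The statement also needs its scope made explicit, because it covers the pooled cohort while several main endpoints are by subtype. The figures of about ±9 and ±7 points for sarcoidosis or IPF/IIP show the order of size only and depend on the borrowed 1995 mix.

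**What to change.** In Section 5.7, replace the ±5% at n = 350 by a half-width of ±5.2 percentage points at n = 350 and ±4.0 at n = 600, for an event with 50% frequency at 95% confidence. Alternatively, keep ±5 and tie it to 385 evaluable patients. In either case, say that the numbers are patients in the analysis set rather than patients enrolled, and that the figure refers to all ILDs pooled. One further sentence should say that intervals within a subtype will be wider; the sarcoidosis and IPF/IIP figures above could serve as an example if labelled as an illustration.

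The cost is a change of wording. It needs no extra patients and no change to data collection or analysis. The precision quoted for the first-year sample becomes slightly less favourable.

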## 1. Introduction

Interstitial (or diffuse parenchymal) lung diseases (ILDs) represent a large, heterogeneous group of more than 200 different entities, most of which are classified as rare diseases [1–3]. They are defined as lung diseases that affect the alveolar structures, the pulmonary interstitium, and small airways. A diagnosis of an ILD relies mainly on the combination of clinical, radiological, and pathological criteria, which should be explored in a multidisciplinary board. Among the ILDs, the most important are sarcoidosis, idiopathic pulmonary fibrosis (IPF), hypersensitivity pneumonitis (HP), also called extrinsic allergic alveolitis (EAA), ILD as a manifestation of connective tissue disease (CTD), and drug-induced ILD and pneumoconiosis [2, 3]. The majority of ILDs are idiopathic and include the group of idiopathic interstitial pneumonias (IIPs) (Figure 1). Only about one in three cases of ILD have an identifiable cause [1].

Despite being rare diseases, the recent Global Burden of Disease Study reported that interstitial lung diseases rank in 40th position of all diseases regarding global years of life lost in 2013, which represents an increase of 86% compared to 1990 [4]. The most common ILD, IPF, has a poor prognosis with median survival of 2-3 years from diagnosis [5]; for other forms of ILD, prognosis depends on the underlying and/or accompanying disease(s) but may be similarly poor. For example, recent data on sarcoidosis, which is usually considered a more benign ILD, indicates a considerably higher mortality rate than previously reported [6]. Much remains unknown or debatable for many ILDs because there is a lack of data on the prevalence, incidence, and mortality rates of this group of lung diseases as well as clinical evidence guiding optimal management, healthcare utilisation, and their associated healthcare costs [1].

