### 5.5. Patient Withdrawal/Discontinuation

Patient drop-out or withdrawal may occur for the following reasons and will be recorded.

Withdrawal by the investigator due toadministrative reasons;lost for follow-up.

Withdrawal by patient from the study due toown request;specific request of the sponsor.

In the event that a patient is withdrawn, the registry termination page in the eCRF will be completed, including information on the date of the withdrawal, who initiated the withdrawal, and the reason for withdrawal, if known. Reasonable effort will be made to contact any patient lost to follow-up during the course of the registry to retrieve any outstanding data.

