^†^Radiation was also included in the Italian and SEPAR registries.

^‡^Coal worker's pneumoconiosis was excluded in the Flemish, Italian, and SEPAR registries.

Adapted from the European Lung White Book Chapter 22 [18].

**Table 2 tab2:** ILD patients and subtypes^*∗*^ eligible for enrolment in the EXCITING-ILD registry.

Idiopathic interstitial pneumonias (IIPs)	Idiopathic pulmonary fibrosis (IPF) Idiopathic nonspecific interstitial pneumonia (NSIP) Desquamative interstitial pneumonia (DIP) Respiratory bronchiolitis-associated interstitial lung disease (RB-ILD) Cryptogenic organising pneumonia (COP) Idiopathic lymphoid interstitial pneumonia (LIP) Acute interstitial pneumonia (AIP) Rare forms of IIPs (e.g., pleuropulmonary fibroelastosis) Nonclassifiable IIP

Granulomatous lung disease	Sarcoidosis Berylliosis Other (e.g., involvement in chronic inflammatory liver and gut diseases, except EAA)

Hypersensitivity pneumonitis (extrinsic allergic alveolitis (EAA))	Farmer's lung Bird keepers' lung disease Origin unknown Other

Rheumatic and connective tissue diseases with pulmonary involvement such as	Connective tissue disease (subtype) Vasculitis Rheumatoid arthritis

Pneumoconiosis	Asbestosis Silicosis Other

Other forms	Pulmonary lymphangioleiomyomatosis Pulmonary Langerhans' cell histiocytosis Pulmonary alveolar proteinosis Eosinophilic pneumonia Post-ARDS fibrosis

Drug-related	

Radiotherapy associated	

Fibrosis in emphysema patients without signs of other ILDs (CPFE)	

Others	

Not classifiable	

^*∗*^For each subtype it will be queried whether or not a diagnosis of concomitant emphysema in ILD was made.

**Table 3 tab3:** List of variables to be documented (if available) at baseline and scheduled visits.

	Baseline	Follow-up every 6 months
*Eligibility criteria*	*✕*	

*Demographic/sociodemographic data*	*✕*	
Gender, country of birth, place of residence with zip code, profession, year of birth, and date of ILD first diagnosis if available	*✕*	
Weight and height, BMI	*✕*	*✕*
Incapacitated for work caused by ILD	*✕*	*✕*
Health insurance coverage	*✕*	*✕*

*Risk factors*	*✕*	
Smoking status, profession, familial ILD, HIV		

*Profession*	*✕*	*✕*
Profession, in work, unemployed, student, retired, other, incapacitated for work caused by ILD, disease-related absent days past six months		

*Comorbidities with prognostic impact*	*✕*	*✕*
Gastroesophageal reflux (treatment), pulmonary hypertension (treatment), emphysema		

*Disease-related data*		

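### The only analysis set the article defines requires a visit after baseline; if time to death is analysed in it, patients who die before the first 6-monthly visit drop out and survival is overestimated

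*Protocol article*

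**What the plan says.** Section 5.7 of the protocol article (paragraph on sample size) fixes the analysis population: "All subjects with at least one documented postbaseline visit will be entered into the full analysis set (FAS". It adds "Further analysis sets may be defined in the SAP", but the article names no other set.

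Table 3 gives the visit schedule after baseline: "Follow-up every 6 months".

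The main endpoints in Section 4 include "the outcome of different types of ILDs and of ILD-related therapies measured as time to death". Section 5.7 gives the method: "Time to death will be analysed by means of Kaplan-Meier survival analysis". That sentence names no population and no time origin.

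The article states no exception for a patient who dies before the first follow-up visit.

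**The concern.** Membership of the set depends on something that happens after enrolment and that a patient must normally be alive to do. A patient enrolled in January who dies in April has no follow-up visit. Read literally, the rule removes that patient, although the death is the event that the endpoint counts. Those who remain are known to have survived to their first visit, so the curve is flat over that interval by construction (immortal time) and too high afterwards.

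The error always goes in the same direction and is larger where early mortality is higher. The registry intends to describe outcomes by ILD type and to study prognostic factors, so levels of survival and differences between types are both affected. Section 6 relies on consecutive recruitment to limit selection bias. A condition of this kind would bring selection back at the analysis stage, and on the outcome itself.

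**Working it through.** The article gives no figure for the size of the full analysis set or for early deaths, so there is no stated number to reproduce. The check asks how large the effect is if Kaplan-Meier is run on this set.

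**Inputs**
- First follow-up visit at 0.5 year (Table 3).
- IPF: "poor prognosis with median survival of 2-3 years from diagnosis" (Section 1).
- Medians of 5 and 10 years for milder mixes of ILD: assumed, not in the article.
- Constant hazard, with time counted from enrolment: assumed.

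**Formulas**, with m the median in years
- True survival: S(t) = 0.5^(t/m).
- Share who die before the first visit, and so are excluded: 1 − S(0.5).
- Curve in the restricted set, for t ≥ 0.5: S(t)/S(0.5).
- Median in the restricted set: solve 0.5^((t − 0.5)/m) = 0.5, which gives t = m + 0.5.

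Worked case, m = 2: S(0.5) = 0.5^0.25 = 0.841, so 15.9% are excluded. S(1) = 0.707, and the restricted set shows 0.707/0.841 = 0.841.

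| Median m (years) | Excluded | 1-year survival, true → restricted | Overstated by | 2-year survival, true → restricted | Median, true → restricted |
|---|---|---|---|---|---|
| 2 (IPF, lower) | 15.9% | 70.7% → 84.1% | 13.4 points | 50.0% → 59.5% | 2.0 → 2.5 |
| 3 (IPF, upper) | 10.9% | 79.4% → 89.1% | 9.7 points | 63.0% → 70.7% | 3.0 → 3.5 |
| 5 (assumed) | 6.7% | 87.1% → 93.3% | 6.2 points | 75.8% → 81.2% | 5.0 → 5.5 |
| 10 (assumed) | 3.4% | 93.3% → 96.6% | 3.3 points | 87.1% → 90.1% | 10.0 → 10.5 |

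**Visit timing.** The first visit will not fall exactly at 6 months. In a simulation with the visit spread evenly over months 3 to 6, the share excluded is 12.2% (m = 2) or 8.3% (m = 3), and 1-year survival reads 80.5% or 86.5%. Spread over months 6 to 9, the share is 19.5% or 13.4%, and 1-year survival reads 87.7% or 91.7%. The effect changes in size but not in direction.

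**Differences between types.** Compare a type with a 2-year median and one with a 10-year median. The true 1-year difference is 93.3 − 70.7 = 22.6 points. In the restricted set it is 96.6 − 84.1 = 12.5 points. Under constant hazards, a hazard ratio estimated from the later deaths would not change. What moves are the survival percentages and medians that a descriptive registry reports.

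**The case against.** The strongest objection is that the link between the survival analysis and this set is not written down. The Kaplan-Meier sentence names no population, the set is defined in the sample-size paragraph, and other sets are left to an SAP that exists but is not shown. It is also undefined whether a report of death would count as a documented visit. This stands, and it makes the point conditional. It does not remove the point: the article defines only this set, assigns survival to no other, and exempts no early death.

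The size is also open to challenge. The IPF median runs from diagnosis, whereas the registry enrols patients already diagnosed. The hazard is assumed constant. IPF is only part of the cohort: IPF/IIP makes up 17 to 42% in the registries of Table 1. If time were counted from diagnosis, the formula above would not apply as it stands. All of this holds, so the IPF rows must not be read as a figure for the whole registry.

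A reader might infer more than the article supports:
- **A contradiction with "Subjects with incomplete data will be included in the analysis".** That sentence goes on to reporting missing values for each variable. It can hold together with a rule on who belongs to a set.
- **That death is not recorded.** Section 5.5 describes the termination page as "including information on the date of the withdrawal, who initiated the withdrawal, and the reason for withdrawal, if known", and Table 3 as shown has no vital-status item. But the article condenses the full protocol, Table 3 covers baseline and scheduled visits, and death is an endpoint rather than a withdrawal. Its absence here shows nothing.
- **That early losses without death add to the overestimate.** Such patients would be censored and contribute almost nothing to the curve. Dropping them costs numbers but adds nothing to the survival bias, and does not offset it.
- **That a particular eligible subtype, such as acute interstitial pneumonia, drives the effect.** The article lists it as eligible but gives no mortality for it.
- **That baseline data are certainly lost, or that cost results are biased by a known amount.** Section 5.7 also says that all collected data are analysed descriptively, without limiting this to the set, and no cost effect can be calculated.

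**Conclusion.** The point holds in conditional form. The one analysis set that the article defines selects on survival to a follow-up visit, and time to death is not exempted. If Kaplan-Meier is run on that set, survival is overestimated, and the overestimate grows with early mortality.

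The direction follows from the rule itself. The size rests on exponential survival from enrolment and a first visit at 6 months. For IPF at the article's median of 2 to 3 years, about 10 to 13 points are added at 1 year and about 0.5 year to the median. At assumed medians of 5 and 10 years, about 6 and 3 points are added at 1 year. The article does not support the unconditional statement that the registry's survival results will be biased, because the SAP may name another population.

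**What to change.** State in the protocol and SAP that time to death is analysed in all eligible consented patients with baseline data. Deaths before the first follow-up visit count as events, and all other patients are censored at the date last known alive. Use the same population for baseline characteristics, which need no follow-up visit. Keep the postbaseline-visit condition only for change-from-baseline summaries. If the SAP already does this, one sentence saying so settles the matter.

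The cost is a change of wording, with no extra visits. The survival analysis needs a date of death or a date last known alive for every enrolled patient, which time to death requires in any case. Some patients will contribute little follow-up. Reported survival will be less favourable than in the restricted set, by the amount of the bias removed.
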